## STATISTICAL ANALYSIS

Intention to treat (ITT) analyses at patient level will be performed, using mixed logistic/linear regression models, controlling for baseline values, stratification variables, and potential confounders as appropriate. Practice will be modelled as a random effect to allow for the clustering of patients within practices. Patterns of missing data will be explored, sensitivity analysis used to explore the impact of missingness, and imputation of missing data will be used. In a non-inferiority trial where some patients do not comply with treatment as randomised, the difference between the arms can appear reduced and the groups look more similar, leading to the incorrect conclusion of non-inferiority. A per protocol (PP) analysis would analyse individuals based on their compliance with treatment as randomised, excluding non-compliant participants, giving a more conservative estimate of effect for non-inferiority (Piaggio 2006).

However, the exclusion of some participants after randomisation can potentially lead to bias. Therefore we will present both ITT and PP analyses.

We will also undertake a complier-average causal effect (CACE) analysis, another approach to dealing with noncompliance that compares compliant participants in the intervention group, with those in the control group whose characteristics are similar enough to the intervention group compliers to suggest they too would have complied with the intervention, given the opportunity to do so (Angrist 1996, Dunn 2005). Compliance for these analyses in the intervention arm will be defined as completing the first session of the LifeGuide programme within 6 months of recruitment (anticipating 90% plus). The first session will have information about antidepressant treatment, the rationale for attempting withdrawal, and how withdrawal should be attempted under supervision. We would expect patients to benefit from that session even if they do not log on again. Compliance in the control arm will be defined as having consulted the GP/PN to have their antidepressant treatment reviewed within the 6-month follow-up period. For the primary outcome we will report the analyses based on all three approaches and interpret the findings cautiously in light of any differences between approaches that may emerge. This analysis will form the core of the publication of the trial results. No interim analyses will be performed.

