### **2.2 Trial power and sample size**

To have 90% power, with a one-sided alpha of 2.5%, to establish non-inferiority in terms of depressive symptoms within two points (estimated to be the minimal clinically important difference) on the PHQ-9 at 6 months (standard deviation 5.4), we need 155 patients followed up in each arm. Assuming a variable cluster size of between 1 and 7 per practice (mean 3) and an intra-cluster correlation coefficient of 0.012 (from the Health Technology Assessment THREAD trial of treating mild-to-moderate depression in primary care), gives a 1.033 cluster design effect (based on a coefficient of variation of  $1.5/3 = 0.5$ , using the formula of Eldridge). Anticipating 20% do not comply with the intervention and/or are lost to follow-up, we need to randomise  $(155 \times 2 \times 1.036) / 0.8 = 402$  patients (201 per arm) from 134 practices (67 per arm).

Following discussion with the study steering committees and the funder, the sample size was amended to 360 participants. This allows for a correlation between baseline and follow-up scores with a deflation factor of  $1 - \rho^2$ . At the time of review we observed a correlation of 0.47 but were unsure whether this would persist to the end of follow up for all participants. If we assume the more conservative estimate of correlation of 0.26 (the bottom end of the CI), the target sample size to achieve 90% power would 375. We assume the final figure will be somewhere in between 0.26 and 0.47, and that a sample of around 360 will therefore provide us with the necessary 90% power to test reliably for non-inferiority of the intervention in terms of depressive symptoms.

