##### **3.1.3 CACE analysis population**

We will also undertake a complier-average causal effect analysis, which is another approach for dealing with non-compliance that compares compliant participants in the intervention group with those in the control group whose characteristics are similar enough to the intervention group compliers to suggest they too would have complied with the intervention given the opportunity to do so. Compliance for these analyses in the intervention arm will be defined as completing the first session of the LifeGuide programme within 6 months of recruitment (anticipating >90%). The first session will have information about antidepressant treatment, the rationale for attempting withdrawal, and how withdrawal should be attempted under supervision. We would expect patients to benefit from that session even if they do not log on again.

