### **4.4 Primary endpoint**

The primary outcome, that is, the differences at 6 months between intervention and control in depression as measured by the PHQ-9, will be analysed using a linear mixed model, adjusting for duration of depression, past history of depression, age, gender, marital status, no. of dependents, ethnic group, education level, economic position (employment status), and accommodation status, baseline depression score, anxiety score, internet use and clustering, including practice as a random effect. These covariates have been chosen based on their known relationship with the outcome from previous literature.

The model will use all the observed data and makes the assumption that missing PHQ-9 scores are missing completely at random. We will examine the lower limit of the 95% confidence interval to establish non-inferiority.

We will then undertake the same analyses using the per protocol population and the CACE population.

Whilst the ITT analysis will be the primary analysis, we will report the analyses based on all three approaches and interpret the findings cautiously in light of any differences between approaches that may emerge. This analysis will form the core of the publication of the trial results.

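### The SAP's complier (CACE) analysis is written as a refit of the primary model on a subset, which does not identify a complier effect and conflicts with the instrumental-variable paper it cites

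*Combined protocol and SAP*

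**What the plan says.** SAP section 3.1, which defines the analysis populations, has an entry for CACE (3.1.3). It describes an analysis that "compares compliant participants in the intervention group with those in the control group whose characteristics are similar enough to the intervention group compliers", meaning controls who would have complied had they been offered the intervention. It cites reference 6, a paper on identifying causal effects with instrumental variables. Compliance is defined for the intervention arm only, as finishing LifeGuide session 1 within six months of recruitment, and more than 90% are expected to do so.

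SAP 4.4 sets out a linear mixed model with covariates and a practice random effect, and then says: "We will then undertake the same analyses using the per protocol population and the CACE population". ITT is primary, and all three results are to be reported and read cautiously if they differ.

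The protocol (STATISTICAL ANALYSIS) gives the same CACE description and adds a rule that the SAP does not carry over: "Compliance in the control arm will be defined as having consulted the GP/PN to have their antidepressant treatment reviewed" within six months. That rule follows the accounts of both the per-protocol and the CACE analyses and is not tied to either one.

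Neither document names a CACE estimator, its assumptions, or the variables that would pick out similar controls.

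**The concern.** A complier in the control arm is someone who would have completed session 1 if given access. No control patient reveals this, because the protocol's Consent procedure and Intervention arm sections describe web access for the intervention arm only. A dataset cannot be filtered on an unobserved status. An analyst told to run the same model on a CACE population must therefore put something in its place: all controls, look-alike controls chosen by an unstated rule, or controls who had a GP or nurse review. The first and third do not identify the complier effect. The second does so only under an assumption that the SAP does not make.

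If the protocol's review rule is used for both supportive analyses, the per-protocol and CACE analyses select the same patients and fit the same model, so the third approach merely repeats the second.

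SAP 3.1.2 warns that non-compliance can make arms look alike, and that excluding patients after randomisation can bias the comparison. CACE is offered as another way to deal with non-compliance. As worded, it is open to the same selection bias and could give false reassurance. The choice of method would also be left until the data are in hand, which SAP 1.1 says the plan exists to prevent.

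**Working it through.** **The plan's own figure.** SAP 2.2 takes 90% power, a one-sided 2.5% test and a 2-point PHQ-9 margin, and arrives at: "standard deviation 5.4), we need 155 patients followed up in each arm".

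- n per arm = 2 × (1.960 + 1.282)² × 5.4² / 2² = 153.2, so 154. The plan states 155, where t-based power is 90.2%. Reproduced.
- Design effect, with "intra-cluster correlation coefficient of 0.012", mean cluster size 3 and coefficient of variation 0.5: 1 + [(0.25 + 1) × 3 − 1] × 0.012 = 1.033. The plan multiplies by 1.036: 310 × 1.036 / 0.8 = 401.5, so 402. Using 1.033 gives 400.3. The difference does not matter here.

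The only CACE figure in the documents is the anticipated compliance.

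**Bias of a subset refit.** Let π be the complier share, τ the true complier effect (intervention minus control, positive = worse depression), and D the excess PHQ-9 score of non-compliers over compliers that covariates do not explain. The documents do not give D, so 1 to 3 points is assumed.

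- Mean of intervention compliers: μ + τ.
- Mean of all controls: μ + (1 − π)D.
- Subset contrast: τ − (1 − π)D, so the bias is −(1 − π)D.

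If controls are restricted to those reviewed, let g be the share reviewed and d their excess score over the rest, unrelated to complier status. The bias is then −(1 − π)D − (1 − g)d. Taking g = 0.7 and d = 2 (both assumed), the second term is −0.6.

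| Compliance | D | Bias, all controls | Bias, reviewed controls |
|---|---|---|---|
| 90% | 1 | −0.1 | −0.7 |
| 90% | 2 | −0.2 | −0.8 |
| 90% | 3 | −0.3 | −0.9 |
| 80% (assumed) | 1 | −0.2 | −0.8 |
| 80% (assumed) | 2 | −0.4 | −1.0 |
| 80% (assumed) | 3 | −0.6 | −1.2 |

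Negative values favour non-inferiority. The signs follow from the assumptions that non-compliers, and patients who are reviewed, are the more symptomatic. If reviewed patients scored 2 points lower, the 90%, D = 2 entry would be −0.2 + 0.6 = +0.4.

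**Instrumental-variable ratio.** If allocation affects PHQ-9 only through session 1 (the exclusion restriction), the ITT effect is πτ, and dividing by π returns τ.

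**Example with a true complier effect beyond the margin.** Take τ = 2.2, π = 0.9, D = 3. All controls: 2.2 − 0.3 = 1.9. Reviewed controls: 2.2 − 0.9 = 1.3. ITT: 0.9 × 2.2 = 1.98. Instrumental-variable ratio: 1.98 / 0.9 = 2.2. Large simulations for D = 2 and 3 agreed with these formulas to within about 0.01.

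**Precision of the replacement.** The ITT 95% half-width at 155 per arm, the number before inflation for clustering, is 1.96 × 5.4 × √(2/155) = 1.20. Dividing by 0.9 gives 1.34 (factor 1.11), and by 0.8 gives 1.50 (factor 1.25). Power against the 2-point margin with no true difference is about 83% and 74%, compared with 90% for ITT.

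**The case against.** The best defence is that SAP 3.1.3 states the contrast in counterfactual terms and cites an instrumental-variable paper, so a proper complier analysis may be what the authors intend. In 4.4, the same analyses could mean the same outcome, covariates and clustering. This stands as evidence of intent. It does not settle the procedure, because the operative sentence names a population and no estimator, and the two cannot both be followed.

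A reader might infer that no complier comparison can ever be built by choosing controls. The documents do not support that. Selecting controls on covariates could target the complier effect under principal ignorability, meaning that complier status carries no further prognostic information once covariates are known. The gap is that neither this assumption nor the selection variables are stated.

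A reader might also infer that the non-inferiority conclusion depends on the three analyses agreeing. It does not: ITT is primary, and the other results only temper interpretation.

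It can also be said that the review rule belongs to the protocol and may be meant for the per-protocol set. That is fair, and is why the reviewed-controls column is conditional.

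Finally, the instrumental-variable route has its own weakness. Practitioner training and telephone calls (protocol, Intervention arm) may help patients who never log on. If so, ITT divided by compliance is not the complier effect either.

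**Conclusion.** The concern holds for the text as written. SAP 3.1.3 and 4.4 direct a subset refit that does not identify the complier effect without an unstated assumption, and that conflicts with the method cited. This is more than missing detail, but it falls on a supportive analysis.

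At the anticipated compliance the bias against all controls is modest: about 0.1 to 0.3 points towards non-inferiority for assumed gaps of 1 to 3 points, and smaller if compliance exceeds 90%. It reaches 0.7 to 0.9 points if controls are selected by review, under the further assumptions of 70% reviewed and a 2-point excess. An 80% complier share is illustrative only, because the 20% in SAP 2.2 combines non-compliance with loss to follow-up.

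It would go too far to say that the flaw would by itself produce a false claim of non-inferiority. In the example, adding the ITT half-width of 1.20 to 1.9 and 1.3 gives 3.1 and 2.5, both still beyond the margin. The documents show only that the CACE result could look more favourable than it should and is not the independent check it appears to be.

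**What to change.** - Remove CACE from the list of analysis populations in SAP 3.1 and from the sentence in 4.4.
- In their place, specify an instrumental-variable analysis of all ITT patients with an observed 6-month PHQ-9. Randomised arm is the instrument and LifeGuide session 1 within six months is the exposure, set to zero in controls by design. Use the 4.4 covariates and allow for clustering by practice. Two-stage least squares is one suitable estimator; another is acceptable if named in advance.
- State the exclusion restriction, and say that practitioner training and telephone calls may violate it.
- Keep the GP or nurse review definition for the per-protocol set only, and write it into SAP 3.1.2.
- Judge the result against the 2-point margin using the confidence limit on the side of worse depression. SAP 4.4 refers to the lower limit, while higher PHQ-9 scores are worse (SAP 3.4), so the direction of the difference must be stated and the wording reconciled.

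The cost is SAP wording and one standard procedure. LifeGuide already records use automatically (protocol, PROCESS EVALUATION, Quantitative), so no new data are needed. The downsides are an interval about 1.11 times the ITT interval at 90% compliance and dependence on the exclusion restriction.

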### **4.5 Secondary endpoints**

The discontinuation of antidepressants will be evaluated at 6 months as a binary outcome in a mixed logistic regression model, using the same modelling approach and covariates as for the primary outcome.

Analysis of all other secondary outcomes will also be conducted using generalised linear mixed regression models adjusting for stratification variables, the potential confounders listed in 4.4 above and the baseline value of the outcome. These will be evaluated as repeated measures so all models will allow for the clustering of observations within participants over time and of participants within practices.

#### **4.6 Additional analyses**

No subgroup analyses are planned. Any post-hoc analyses will be exploratory only. Health economic analyses will be undertaken and a separate Health Economics Analysis Plan will be prepared.

In accordance with the CONSORT recommendations for cluster randomised trials, we will also report the ICC for the primary outcome.

Due to the COVID-19 pandemic and subsequent lockdown period, it is possible that there may be changes to the key outcomes unrelated to randomisation group. We will therefore look at the scores in each arm in the pre-, peri- and post-COVID periods in the whole study population. We will use descriptive statistics and graphical representations to explore any trends and aim to control for any time varying effect on outcomes in a sensitivity analysis

#### **4.7 Safety reporting**

A listing of serious adverse events (SAEs) will be provided for all related/unrelated SAEs. If required, a summary table will also be presented.

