### 6.4.1 Expected Adverse Events:

|                                           |                                                                                                                                                                                                           |
|-------------------------------------------|-----------------------------------------------------------------------------------------------------------------------------------------------------------------------------------------------------------|
| Mild antidepressant withdrawal symptoms   | Likely to occur in around half of patients reducing and stopping their antidepressants. If mild enough to be tolerated by patient, and short-lived (up to two weeks), these do not need reporting as AEs. |
| Moderate to severe withdrawal symptoms    | If severe or prolonged withdrawal symptoms occur, requiring restarting of antidepressant, please report as related and expected AE.                                                                       |
| Relapse of depression or anxiety disorder | May occur in 10-20% of patients over the one year follow-up, requiring restarting of antidepressant. Please report as related and expected AE.                                                            |

The nature or severity of should be considered when making the assessment of expectedness. If these factors are not consistent with the current information available then the AE should be recorded as 'unexpected'.

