### Baseline telephone screening

Patients will be assessed by telephone and excluded if they have any of the exclusion criteria listed above. Exclusion criteria include significant depressive symptoms despite antidepressant treatment, defined as a score of 12 or more on the Patient Health Questionnaire (PHQ-9) (Kroenke 2001) completed over the telephone. The PHQ-9 is a self-complete questionnaire taking approximately three minutes. It measures nine core symptoms of depression based on Diagnostic and Statistical Manual (DSM-IV) criteria and has high sensitivity and specificity in UK primary care (Gilbody 2007).

Patients will also be excluded if they have significant anxiety at baseline, i.e. a score of 10 or more on the 7-item Generalised Anxiety Disorder scale (GAD-7), also completed over the telephone. The GAD-7 is a brief screening instrument for anxiety also validated in primary care (Spitzer 2006). Though originally developed to detect GAD, it also has good sensitivity and specificity for panic, social anxiety, and post-traumatic stress disorders (Kroenke 2007).

If patients score above 0 (i.e. 1, 2 or 3) on the 9th question of the PHQ-9, about suicide/self-harm, they will be excluded from participating, and this information will be relayed to their GP immediately for them to discuss this, preferably with their permission. The information may be relayed without their permission if necessary, after discussion between the researcher, the principal investigator, and the patient.

If patients are excluded at baseline screening due to either a total PHQ-9 depression score of 12 or more, or a score of 1 or more on the self-harm question 9 of the PHQ-9, or a total GAD-7 anxiety score of 10 or more, and they wish to be reconsidered for inclusion at a later date, they may consent to being recontacted in three months to be re-screened. At re-screening, they may be included in the study if those exclusion criteria no longer apply.

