### **1.4.2 Definition of secondary endpoints**

- The PHQ-9 score over the full 12 month period as a repeated measure analysis
- Discontinuation of antidepressants at 6 months
- Antidepressant withdrawal symptoms measured on the Discontinuation Emergent Signs and Symptoms scale (DESS) over the trial period
- Anxiety on the GAD-7 measure of generalised anxiety disorder over the trial period
- Wellbeing scores over the trial period on the Warwick-Edinburgh Mental Wellbeing Scale (WEMWBS)
- Modified version of the Medical Informant Satisfaction Scale (MISS) over the trial period to measure patient satisfaction over the follow-up period.
- Patient enablement measured by the Patient Enablement Instrument (PEI) over the trial period

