## **3.4 Definition of key derived variables**

The PHQ-9 is a self-complete questionnaire taking approximately 3 min to complete. Each item is scored 0-3 with a total possible score ranging from 0-27. Higher scores indicate more severe symptoms.

The Generalised Anxiety Disorder Assessment 7-item version is a self-report measure of anxiety symptoms. Each item is scored from 0-3 with a total possible score ranging from 0-21. Higher scores indicate more severe symptoms.

Discontinuation of antidepressants is deemed to have occurred once the patient has stopped taking them for 2 months. This is a binary outcome (did not discontinue/did discontinue).

The Warwick–Edinburgh Mental Wellbeing Scale (WEMWBS) measures both subjective experiences of happiness and life satisfaction (the ‘hedonic perspective’), and positive psychological functioning, good relationships with others and self-realisation (the ‘eudaimonic perspective’). Each item is answered on a 1 to 5 Likert scale and summed to give a total score ranging from 14 to 70. Higher scores indicate greater wellbeing.

Antidepressant withdrawal symptoms are measured using the Discontinuation Emergent Signs and Symptoms scale, a brief self-report measure on which participants can indicate the presence of, and

changes in, 43 possible antidepressant withdrawal symptoms. The total number of symptoms is summed.

The 29-item 'Medical Interview Satisfaction Scale' (MISS-29) was developed in the USA to assess patient satisfaction with individual doctor-patient consultations and has been shown to be valid and reliable in UK primary care.

The modified Patient Enablement Instrument asks 6 questions about the patients' ability to understand their problems and cope with illness. These are rated on a 7 point Likert scale (0=strongly agree to 7=strongly disagree). A mean overall score can be calculated, with lower scores equating to better enablement.

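### The SAP plans no by-arm count of relapse or of severe withdrawal needing restart, the two non-mild harms the protocol expects; adding one is a cheap improvement

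*Combined protocol and SAP*

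**What the plan says.** SAP 4.7 (Safety reporting) has two sentences: "A listing of serious adverse events (SAEs) will be provided for all related/unrelated SAEs", and "If required, a summary table will also be presented". The second gives no trigger, content or layout by arm, and it follows on from the sentence about SAEs.

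The protocol's list of expected adverse events (6.4.1) says of relapse of depression or anxiety: "May occur in 10-20% of patients over the one year follow-up, requiring restarting of antidepressant. Please report as related and expected AE". Of withdrawal it says: "If severe or prolonged withdrawal symptoms occur, requiring restarting of antidepressant, please report as related and expected AE". Mild, short-lived withdrawal need not be reported.

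The endpoints in SAP 1.4 are PHQ-9 at 6 months (primary), PHQ-9 as a repeated measure over 12 months, discontinuation at 6 months, DESS, GAD-7, WEMWBS, satisfaction and enablement. The DESS endpoint is "Antidepressant withdrawal symptoms measured on the Discontinuation Emergent Signs and Symptoms scale (DESS) over the trial period", and SAP 3.4 scores it simply: "The total number of symptoms is summed". Neither relapse nor restart of treatment is an endpoint.

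**The concern.** The trial sets out to show that antidepressant use can be reduced without depression getting worse (protocol lay summary; SAP 1.2). The harm that bears most directly on that claim is relapse after stopping. The protocol names it, gives an expected rate and asks sites to report it, but the SAP has no planned use for those reports.

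The other planned analyses cover this only in part. PHQ-9 and GAD-7 enter as scores, and a minority with large rises moves a mean only a little. DESS is a count of symptoms, with no severity grade and no link to restarting. Discontinuation is a single status at 6 months: a patient who tapers, relapses and is back on treatment by then is coded like one who never tapered, and a restart after 6 months leaves a recorded success unchanged. Relapses after 6 months do not touch the primary endpoint at all, although the protocol's expected rate is over one year.

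SAP 4.6 makes any post hoc analysis exploratory. A relapse comparison added once results are known would therefore carry little weight.

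**Working it through.** **Inputs from the documents.** SAP 2.2: margin 2 points, SD 5.4, one-sided alpha 2.5%, power 90%, mean cluster size 3, coefficient of variation 0.5, ICC 0.012, 20% non-compliance and/or loss, final N 360, baseline to follow-up correlation between 0.26 and 0.47. SAP 4.4: non-inferiority is judged on a limit of the 95% CI. Protocol 6.4.1: relapse 10-20% over one year.

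**Assumed.** D, the number of PHQ-9 points by which a relapsed patient is worse at 6 months, is not in the documents. The range used is 5 to 12. The two ends of the protocol's relapse range stand for control (10%) and intervention (20%), and all relapses are taken to show in the 6-month score.

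**Reproducing the plan's figures.**
- n per arm = 2 × (5.4 × (1.960 + 1.282) / 2)² = 153.2, so 154 (plan: 155).
- Design effect = 1 + ((1 + 0.5²) × 3 − 1) × 0.012 = 1.033.
- 155 × 2 × 1.036 / 0.8 = 401.5, so 402. With 1.033 it is 400.3, which is immaterial.
- 402 × (1 − 0.26²) = 374.8 and 402 × (1 − 0.47²) = 313.2, matching the protocol's 375 and 313.

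**What the decision rule lets through at N = 360.** Evaluable patients per arm = 360 × 0.8 / 2 = 144.
- SE = 5.4 × √((1 − ρ²) × 1.033 × 2 / 144) = 0.625 (ρ = 0.26) or 0.571 (ρ = 0.47).
- Power at no true difference = Φ(2/SE − 1.96) = 89.3% or 93.9%.
- Largest observed difference that still passes = 2 − 1.96 × SE = 0.78 or 0.88.

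An excess of 10 percentage points in relapse shifts the mean by 0.10 × D, and the probability of declaring non-inferiority is Φ((2 − 0.10 × D)/SE − 1.96). The last column is the largest passing difference divided by D. Ranges run from ρ = 0.26 to ρ = 0.47.

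| D (assumed) | Mean shift, 10% v 20% | Probability non-inferiority declared | Observed excess relapse that just passes |
|---|---|---|---|
| 5 | 0.5 | 67-75% | 15.5-17.6 points |
| 8 | 0.8 | 49-56% | 9.7-11.0 points |
| 10 | 1.0 | 36-42% | 7.8-8.8 points |
| 12 | 1.2 | 25-29% | 6.5-7.3 points |

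**What a by-arm comparison would deliver.** At 10% v 20% one expects about 14 v 29 patients in 144 per arm. The 95% CI half-width is 1.96 × √((p₀q₀ + p₁q₁) × 1.033 / 144):
- 10% v 10%: 7.0 points
- 10% v 20%: 8.3 points
- 20% v 20%: 9.4 points
- 20% v 30%: 10.1 points

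Two-sided 5% power for 10% v 20% is about 65%. This applies the PHQ-9 design effect to a binary outcome, which is also an assumption.

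**The case against.** The best case for the plan is that it is far from silent on these harms. Withdrawal symptoms are a named secondary endpoint, modelled by arm. PHQ-9 is analysed over the full 12 months as well as at 6, and GAD-7 is compared too. Early restarts partly enter the discontinuation endpoint. A relapse that is life-threatening or leads to admission is an SAE and will be listed. All of this stands. A reader might infer that relapse and withdrawal are never compared by arm in any form, but the documents do not support that. What is missing is a comparison of patients who had the event.

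A reader might also divide the margin by an assumed rise and infer that the design can hide a relapse excess of 20% (2/10) or 25% (2/8). That is wrong. Those values put the true difference at the margin, where non-inferiority is declared only about 2.5% of the time, because the confidence limit decides. The 8- and 10-point rises are themselves assumptions. At a 10-point rise, a doubling of relapse would fail the test more often than pass it.

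Two objections to the remedy also stand in part. PHQ-9 of 12 or more is the protocol's telephone screening exclusion, not a definition of relapse: a change from 11 to 12 counts and one from 1 to 11 does not. At 3 months the score may reflect tapering or withdrawal. And the data schedule has no adverse event item, so those counts rest on what patients and practitioners report.

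**Conclusion.** The point holds as a cheap improvement; it is not a fault in the primary analysis. The protocol's expected non-mild harms have no planned by-arm event comparison unless a case is graded serious. The scores that are compared could miss a doubling of relapse with material probability: from about 67-75% if relapsed patients are 5 points worse at 6 months down to 25-29% if they are 12 points worse.

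These figures rest on 144 evaluable patients per arm, SD 5.4, design effect 1.033, correlation 0.26 to 0.47, and the assumed 5-12 points. If relapsed patients restart and partly recover by 6 months, or relapse later, the 6-month mean moves less and the chance of passing is higher. The documents do not show that relapse will be higher in the intervention arm. They show only that the plan would not report whether it was.

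**What to change.** **SAP 4.5.** Add, as a descriptive secondary analysis, the by-arm proportion with PHQ-9 of 12 or more at 6 months and at 12 months, with denominators, a risk difference and a 95% CI that allows for practice. Describe 12 or more as the protocol's screening cut-off for significant symptoms, not as relapse. Show 3 months separately, because tapering and withdrawal may affect it.

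**SAP 4.7.** Add by-arm counts of patients with each adverse event class the protocol asks sites to report: relapse, and severe or prolonged withdrawal requiring restart.

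**Cost.** Two tables. The PHQ-9 table uses scores already scheduled at 3, 6 and 12 months; the adverse event table is only as complete as the reports received. With a half-width of about 7-10 points this is not a powered test and should not be presented as one. Adverse event reports may be more complete in the intervention arm, since only that arm has psychological practitioner calls, so the scheduled PHQ-9 comparison should carry the weight. Both additions should be fixed before outcomes are seen by arm.
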